##### Exercise Class Format

The PEP element of the intervention, facilitated by the physiotherapists, will follow a group-based format (maximum participants per group, n = 10) similar to the 'Back to Fitness' programme [23] used in the recently published MRC-funded UK BEAM trial [24]: two of the research team (DB, PG) are experienced in this approach as coordinators of the Northern Ireland Regional Centre for the UK BEAM trial. Participants will attend the Research Institute once a week for 6 weeks for a supervised group exercise session lasting for one hour. The exercise programme will consist of a 10-minute warm-up, a combination of core strengthening, flexibility and cardiovascular exercise using a series of 'exercise stations', and a 10-minute cool down and period of relaxation. The added benefit of this particular programme is that the physiotherapist is available to monitor, advise and encourage participants according to their individual treatment goals and exercise capabilities, and to help participants identify which exercise(s) they could realistically continue independently of the treatment sessions, i.e. foster the development of self-management strategies, and improve self-efficacy. Physiotherapists will also advise participants on correct exercise technique, and review and update treatment goals accordingly as the programme progresses. To identify and combat illness behaviours, during the classes physiotherapists will use a biopsychosocial approach to management, based on cognitive behavioural therapy (CBT) principles [23,24]. Each participant will monitor their own progress by documenting exercise progression in their Exercise Class Record Card during each class. This Record Card will also act as a reminder of their individual short term and long term goals, which can be updated with the physiotherapist during the six week class.

##### Education component

There is no separate education intervention/session in this study. Instead, various educational components will be incorporated into the main intervention using a CBT approach. During the baseline assessment each participant will receive a copy of 'The Back Book' [25], to reinforce the message to remain active despite pain, and develop positive coping strategies in the event of an exacerbation of symptoms. Messages from 'The Back Book' [25] will be placed on the walls in the gym and waiting area in order to reinforce key points. During each exercise session the participants will be given a 'Tip for the Day' based on the 'Back to Fitness' programme.

At the beginning of the six week exercise intervention, each participant will receive a home exercise programme containing photographs of the exercises performed during the class, along with information on warm up and cool down. Exercise/activity will gradually be incorporated into the individual's daily routine, as identified in their short and long-term goals during their baseline assessment. Participants will be encouraged to accept responsibility for determining and carrying out their weekly programme of activity. Adherence with the supervised exercise programme will be recorded as the number of sessions attended. Adherence with activity outside of the supervised exercise session will be captured using an activPAL™ professional physical activity logger (PAL technologies, Glasgow, UK) [26] and a structured activity logbook completed by the participant.

#### Telephone helpline

At the end of the structured exercise ± manual auricular acupuncture treatments (week 7), participants will be advised to continue with daily self-directed exercise/activity as agreed with the therapist. A free telephone helpline will also be available three times per week for a two-hour period for a further six weeks for participants who feel that they need advice or support from the therapist, or to answer any other queries or concerns participants may have. Participants' use of this helpline will be closely monitored and calls recorded and at the end of this phase (week 13), each participant will receive a telephone follow-up call from their therapist to provide advice on exercises and functional activities as appropriate, to reinforce the value of exercise adherence, and if necessary to re-evaluate treatment goals.

#### Auricular acupuncture

Prior to each exercise class, participants in treatment group A will receive manual AA (using conventional auricular stud needles). The stud needles consist of a vertical shaft which inserts into the ear, and an external component which is a horizontal circular piece of metal that sits flat onto the surface of the ear; this flat circle is then covered with a small plaster. For each participant receiving manual AA, a stud needle will be inserted at three specific auricular acupuncture points (see Figure 2). Participants will be asked to manually stimulate the needles every three waking hours, or as required for their pain, and to record this in their daily activity logbook. They will be asked to remove the needles after 48 hours [14] and retain for safe disposal by the therapist during the next treatment session.

**Figure 2 F2:**
[figure not shown]
**Auricular acupuncture needles and their placement on the outer ear.** Image of auricular needles courtesy of Scarborough Acupuncture supplies, Somerset, United Kingdom.

#### Experience and Training of Physiotherapists

Two chartered physiotherapists with experience in musculoskeletal physiotherapy and acupuncture will carry out all treatments. Only physiotherapists who have recognised acupuncture training and are members of Association of Acupuncturists in Chartered Physiotherapy (AACP) will be recruited. In addition, each physiotherapist will undertake 3.5 days of training on auricular acupuncture, baseline assessment (including goal setting), and practicalities of running the exercise class. Physiotherapists will be trained in CBT principles by a member of the UK BEAM trial [24] research team (PG). Treating physiotherapists will meet with the research team on a monthly basis to provide an update on the stage of the trial and highlight any potential issues. A member of the research team will monitor the PEP baseline assessments, exercise classes and acupuncture interventions on an ongoing basis.

### Aim and Objectives

To evaluate the feasibility of an RCT exploring the effects on clinical outcomes and exercise adherence of adding manual AA to an individually tailored and supervised exercise programme, when compared to the exercise programme alone.

To determine the feasibility of the trial procedures and establish the most efficient and effective design for a larger RCT by:

(i) Identifying the rate of participation and referrals from the various recruitment routes;

(ii) Determining the actual numbers recruited, adherence and drop out;

(iii) Piloting the methodological procedures;

(iv) Identifying participants' use of a free telephone advice and support service;

(v) Completing a qualitative exploration of the trial procedures and design;

(vi) Confirming training and monitoring requirements for a main trial; and,

(vii) Identifying a crude approximation of the effect size of each treatment package.

### Outcome measures

A number of outcome measures will be collected at week 1 (baseline), and week 7 (end of scheduled exercise ± manual AA) by a blinded assessor as part of the scheduled intervention, and by post at week 13 and at 6 months after initial randomisation (except for the Readiness to Change Questionnaire, the Holistic Complementary and Alternative Health Questionnaire and the Exit Questionnaire). The uptake of the free telephone advice and support service, available between weeks 8–13, will be monitored to establish the value of such a service in a future RCT. Participants in treatment group A will be asked to record in their daily activity logbook how often they manually stimulated the stud needles during the 48 hour treatment period, and all participants will also be asked to record any changes in their analgesic intake during the trial. All outcome measures data will be securely stored and analysed once the trial is complete. Treating physiotherapists will be made aware of the results of the Readiness to Change, Back Beliefs, Fear Avoidance Beliefs Questionnaires and the General Perceived Self-Efficacy Scale, in order to adapt the PEP accordingly.

#### Baseline Questionnaire

This has been developed by the research team to collect information from participants concerning any previous CAM treatment received, any perceived difficulties in adhering to exercise for their low back pain, and their treatment expectations.

#### Readiness to Change Questionnaire

Participants are asked to assess their current levels of physical activity participation. This questionnaire [27] will be collected at week 1 (baseline) only, and used as a predictor of compliance.

#### Visual Analogue Scale (VAS) (0–10 cm)

The VAS is widely used within the clinical setting, and demonstrates acceptable reliability, particularly when used with the same individual [28]. Since such a scale only assesses one dimension of pain, it is recommended that both the bothersomeness and intensity of pain are captured within the assessment, and an average score recorded [28,29]. Participants will be asked to rate their level of back pain and leg pain on average over the past week.

#### Oswestry Disability Questionnaire (ODQ)

The ODQ [30] is a valid and reliable measure of pain and physical function in those with LBP [29-31]. It consists of 10 sections, each with six levels that assess the individual's limitations in various activities of daily living (maximum score in each section = five points): the sum of all sections is divided by the total possible score and the result multiplied by 100 to generate a percentage disability score. Values range from 0 (best health state) to 100 (worst health state) with an average score of 43% identified for chronic back pain participants [30,31]. A minimum clinically important change of 4% has been recommended [32].

#### International Physical Activity Questionnaire (IPAQ-Short Form)

This is a self- or telephone-administered physical activity recall questionnaire, which asks the participant about the time they spent being physically active in the last seven days [33]. Extensive reliability and validity testing across 12 countries indicate that it is a viable method of monitoring population levels of physical activity globally for populations of 18–69 years of age.

#### Physical activity monitoring (ActivPAL™ Professional Physical Activity Logger, PAL technologies, Glasgow, UK)

This is an activity monitoring device that is capable of recording steps taken, cadence, time spent lying/sitting, standing and stepping under free-living conditions [34,35]. The ActivPAL™ professional physical activity logger is a small credit card sized device worn on the anterior thigh. Participants will be shown how to attach the device on the anterior aspect of their dominant thigh, at exactly one third of the distance between the superior pole of the patella and the anterior superior iliac spine, by the outcome assessor. The device will be attached using PALstickies™ and reinforced with Vulcan fixation tape (Mobilis Healthcare Group Limited, Oldham, Lancashire, UK). Exact replacement of the monitor will be assured by using a semi-permanent pen to mark above and below the monitor once accurately placed, or by using a tape measure. Each participant will be asked to wear the activPAL™ professional physical activity logger for seven consecutive days at each time point to establish if there have been any changes in participants' activity levels during the course of the trial. Data will be explored to see if this device provides a useful outcome tool to measure free-living activity in CLBP, when compared with the more conventional daily activity logbook.

#### Daily activity/analgesic intake log-book

Participants will be asked to keep a logbook of their daily analgesic intake along with any changes in the strength/type of medication taken for their LBP. Daily exercise/activity will also be recorded in this logbook for comparison with the data generated by the activity monitor, along with any other treatment received. In addition, this logbook will be used by participants in treatment group A to record how often they manually stimulate the stud needles during each 48-hour auricular acupuncture treatment.

#### Holistic Complementary and Alternative Health Questionnaire

This is an 11-item scale, with six items relating to beliefs about the scientific validity of CAM, and five to beliefs about holistic health (HH) [36]. It is reported to have good test-retest reliability, and internal validity. Responses to each item are made using a six-point response format (strongly agree – strongly disagree). This will be collected at baseline and six months after randomisation to establish if there have been any changes in participants' beliefs of CAM and HH.

#### Fear-Avoidance Beliefs Questionnaire (FABQ)

This is a 16 item self-report questionnaire that specifically focuses on participants' beliefs about how physical activity (5 items) and work (11 items) affect their low back pain [37]. These data will be collected at baseline, at weeks 7 and 13, and 6 months after randomisation. The treating physiotherapists will be made aware of the results of the FABQ prior to commencing the exercise programme, in order to adapt the PEP accordingly. In order to limit respondent burden, participants will only be asked to complete the physical activity section (five items). This decision was made following analysis of pre-pilot data that showed low work section scores. A similar method was used in the UK BEAM trial [24].

#### Back Beliefs Questionnaire

This questionnaire [38] was developed with the aim of measuring an individual's beliefs about the inevitable aspects of the future as a consequence of low back pain. Higher scores indicate more positive beliefs, and less likelihood of absence from work. It consists of 14 questions, five of which are irrelevant and only included to distract the patient (Questions 4, 5, 7, 9, 11). The overall score is generated from the remaining nine questions. In order to limit respondent burden the participants will only be asked to complete the nine questions used to generate the overall score (therefore questions 4, 5, 7, 9, 11 will be omitted). A similar method was used in the UK BEAM trial [24].

#### General Perceived Self-efficacy Scale

The construct of Perceived Self-efficacy is the belief that one can perform novel or difficult tasks, or cope with adversity in various domains of human functioning [39]. Self-efficacy is an important factor in the self-management of chronic conditions and is highly correlated with disability [40]. This scale consists of ten items to assess this construct. In samples from 23 nations, Cronbach's alphas ranged from 0.76 to 0.90 [37].

#### EuroQol-5D

The EuroQol-5D [41] is a self-administered questionnaire that assesses the participant's health-related quality of life using a core set of five health-related quality of life items [42]. Its validity and reliability are supported, and it has been recommended for use in low back pain research [43]. For the UK population, an average weighted health index of 0.86 and self-rated health status of 82.48 have been reported in the literature [44]. Use of this outcome along with the information collected on use of health care resources will facilitate a cost-utility analysis of the trial interventions.

#### APEP Participants' Use of Health Care Resources

This questionnaire was designed by the trial team, in conjunction with a Health Economist.

#### Exit Questionnaire

Patient satisfaction is an important outcome within the field of healthcare. Since there is no single measure preferred within the literature [29], a general assessment of satisfaction [13] will be included in the exit questionnaire. The perceived benefit of treatment to participants, in relation to whether they achieved their initial treatment goals or not, along with any change in analgesic intake, will also be collected by this questionnaire. This will be collected 6 months after randomization only.

### Sample size

No sample size calculation has been carried out as this study aims to identify the referral rates of CLBP participants within the catchment area of the study site. Recruitment will be on a consecutive basis from participating practices, physiotherapy waiting lists and the general public, and will enable the researchers to estimate expected recruitment rates from each of these sources for the main RCT. The researchers aim to enrol eight cohorts of participants, each containing a maximum of n = 10 participants (total n = 80 participants), with randomisation to treatment taking place by cohort. Based on the results of previous trials investigating exercise or acupuncture for LBP, a 30% drop-out rate is anticipated between the beginning of treatment and the follow-up, so it is anticipated that n = 56 participants will complete the trial. The trial statistician is satisfied that this sample size will be sufficient to refine the study protocol, perform a power analysis, and establish the number of participants needed for the main RCT.

### Randomisation

Recruitment and flow of participants through the trial is represented in Figure 1. In accordance with recognised procedure, a computer-generated random allocation sequence will be prepared centrally prior to participant enrolment. This sequence will be used to allocate participants by cohort to one of two treatment groups-A or B. Treatment group A will receive PEP plus manual auricular acupuncture. Treatment group B will receive PEP alone.

The random allocation sequence will be generated by the trial statistician who will not be involved in the administration of treatment or collection of outcomes. The trial statistician will also ensure concealment of treatment allocation by placing individual random assignments into serially numbered sealed opaque envelopes.

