Fluency in English (verbal and written)	Participants with acute (< 6 weeks) or subacute LBP (6–12 weeks), provided that they have experienced < 3 LBP episodes during the previous 12 months
Access to a telephone (for follow-up support)	Previously received auricular acupuncture
Participants categorised as 'low' or 'moderate' activity levels on the International Physical Activity Questionnaire (IPAQ)	Participants with any confounding conditions such as a neurological disorder or currently receiving treatment for cancer
	Road traffic accident causing LBP
	History of psychological or psychiatric illness
	Participants having multiple body and/or ear piercings
	Fear of needles

** In accordance with the Clinical Standards Advisory Group (1994) [21] and the Royal College of General Practitioners Guidelines (Waddell et al., 1999) [22], participants presenting with any or all of the following criteria indicative of radicular pain will be excluded from the study:

(a) unilateral pain usually worse than back pain;

(b) pain generally radiating to the foot or toes;

(c) numbness or paraesthesia in the same distribution;

(d) reduced straight leg raise that produces leg pain;

(e) motor, sensory or reflex change limited to one nerve root.

For all methods of recruitment, once we receive confirmation that they are medically fit to participate in the trial, participants will receive a trial information pack from the lead researcher, be screened by phone, and if eligible an appointment will be made for baseline assessment one week later. During this appointment, the trial procedures will be explained in detail and written informed consent will be obtained. Participants who provide written informed consent will then be randomised, by cohort, according to Figure 1. In order to investigate whether treatment preference has any influence on outcomes, prior to randomisation each participant will be asked which treatment (A or B) he/she would prefer to receive.

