### Interventions

#### Personalised and supervised Exercise Programme (PEP)

##### Baseline Assessment and Goal Setting

Prior to the start of the PEP, each participant will attend the University's Health and Rehabilitation Sciences Research Institute (Jordanstown campus) for a baseline assessment (week 1, Figure 1). This will consist of: an individual consultation with one of two chartered physiotherapists (to discuss the content and aims of the PEP); an assessment of the participant's current level of activity, exercise capabilities and perceived barriers to recovery; recording of the participant's treatment expectations, and any previous CAM treatment; a brief lumbar spine assessment to rule out specific LBP (see Table 1 for exclusion criteria for radicular pain) [21,22]; discussion and agreement, between the therapist and the participant, on short and long-term treatment goals. The aim of agreeing such goals is to gradually include activities or postures which the participant has been avoiding because of their LBP, as well increasing their general activity/exercise levels. Each participant will be asked to document their agreed short term and long term goals in their logbook and the exercise class Record Card. The physiotherapist will emphasise to the participants that the supervised PEP classes are a stepping-stone to self directed activity and will emphasise some of key messages from the Back Book (see below) on how to self manage their back pain.

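### Allocation is concealed with individual assignments although whole cohorts are randomised, and the article does not say that the arm stays hidden until a cohort is closed

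*Protocol article*

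**What the plan says.** The protocol article describes allocation by cohort in several places. Under Participants: "Participants who provide written informed consent will then be randomised, by cohort, according to Figure 1". Under Sample size: "with randomisation to treatment taking place by cohort", with eight cohorts of at most 10 people, 80 in total. Under Randomisation: "This sequence will be used to allocate participants by cohort to one of two treatment groups-A or B". The Statistical methods section calls the design cluster randomised and plans a mixed effects model for that reason.

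The concealment device is described in the second paragraph of Randomisation. The trial statistician is to conceal allocation by "placing individual random assignments into serially numbered sealed opaque envelopes".

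Four other statements bear on the point:

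- Under Participants, consent comes before randomisation, and "prior to randomisation each participant will be asked which treatment (A or B) he/she would prefer to receive".
- Under Sample size: "Recruitment will be on a consecutive basis from participating practices, physiotherapy waiting lists and the general public".
- Under Baseline Assessment and Goal Setting, the visit with one of two physiotherapists includes "a brief lumbar spine assessment to rule out specific LBP", which applies the radicular-pain exclusion.
- Under Blinding, neither participants nor physiotherapists can be blinded to treatment.

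The article does not say when an envelope is opened relative to the filling of a cohort. Figure 1, to which the Participants section refers for the flow, is not available in the text reviewed.

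**The concern.** Serially numbered envelopes with individual assignments are a device for trials that randomise individuals. There, opening one envelope says little about the next. In a cohort-randomised trial all members of a cohort share one arm, so the first opened assignment fixes the arm for the rest. Concealment then depends on whether anyone can still join, or still be assessed, after that opening.

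If that could happen, four things would be at risk:

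- **Selection into the cohort.** A person who knows the arm may accept or decline because of it, and an examiner who knows it makes the last exclusion decision.
- **The preference question.** It is to be analysed against outcomes and is meaningful only if asked before the arm is known.
- **Self-reported baseline scores.** The ANCOVA conditions on these. A blinded assessor does not protect answers given by a participant who already knows the arm.
- **Participation and recruitment rates.** These are a stated feasibility objective, and knowledge of the arm can change who joins.

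Neither baseline adjustment nor a mixed model can be relied on to undo selection of this kind. Because this study pilots procedures for a main trial, a flaw here could be carried forward.

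**Working it through.** **The plan's own figures.** From Sample size: 8 cohorts x 10 = 80 enrolled, and 80 x (1 - 0.30) = 56 expected completers. Both reproduce. The point disputes neither.

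**Inputs.** Number of cohorts k = 8 and maximum size m = 10 (Sample size). The Abstract instead gives k = 4 and m = 20, which is also 80, so both are carried through. The allocation ratio is not stated; simple 1:1 is assumed here.

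The wording can be read in three ways.

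**Reading 1: the envelopes hold independent individual assignments.** The probability that all m members of a cohort fall in the same arm is 2 x 0.5^m.

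- m = 10: 2 x 0.5^10 = 0.00195, about 0.002.
- m = 20: 2 x 0.5^20 = 0.0000019.

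Cohorts would almost never be of one arm. Individual assignment and allocation by cohort therefore cannot both be literal. Under this reading, opening one envelope would reveal nothing about the others. The fault would be a contradiction with the by-cohort design and its clustered analysis, not predictability.

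**Reading 2: the envelopes hold the cohort's shared arm and are opened as each person consents.** There are k independent allocations. The number of participants whose arm is fixed by an earlier opening is k x (m - 1).

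- 8 cohorts of 10: 8 x 9 = 72 of 80 (90%).
- 4 cohorts of 20: 4 x 19 = 76 of 80 (95%).

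These are upper bounds for full cohorts in which every later member enters after the first opening.

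**Reading 3: the cohort's assignment is opened only after all members have consented and been assessed.** The number exposed is 0 of 80. Concealment holds, but separate envelopes per person then serve no purpose, and the text does not state this safeguard.

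| Reading | Consistent with allocation by cohort? | Arm known in advance (8 x 10) |
|---|---|---|
| Independent individual assignments | No | Not applicable |
| Shared arm, opened person by person | Yes | Up to 72 of 80 |
| Shared arm, opened when cohort is closed | Yes | 0 of 80 |

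Under each reading the sentence on envelopes needs changing: in the first it contradicts the design, in the second it fails to protect it, and in the third it leaves out the rule that does the protecting.

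**The case against.** The strongest reply is that the harmful sequence is nowhere stated. The article gives no time of opening, and individual assignments could loosely mean separately sealed ones, one per cohort. Consent and the preference question are placed before randomisation. Read literally together with randomisation by cohort, that order has every member consent and state a preference before a single allocation is made. When and by whom an envelope is opened is also operational detail that a condensed article may leave to the full protocol.

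Much of this stands, and it rules out several stronger conclusions that a reader might draw:

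- **That 72 of 80 participants would be enrolled with the arm known.** This is only the ceiling under one unstated sequence.
- **That cohorts fill over about 10 weeks with baselines spread across that time.** Even accrual over April 2007 to September 2008 gives 80 / 18 = 4.44 per month and 10 / 4.44 = 2.25 months per cohort. That is a rate of finding people, not the spacing of their baseline visits. Baseline is week 1, there are six weekly classes, and the end-of-treatment assessment is week 7, so baselines must fall close to the cohort's first class.
- **That the six-month follow-up drifts by a similar amount within a cohort.** Members randomised together share a randomisation date.
- **That the envelopes conceal nothing.** An unopened envelope conceals the cohort's arm until it is opened.
- **That GPs can steer enrolment, or that the physiotherapist knows the arm at the lumbar examination.** Nothing says that GPs learn allocations, and being unblinded to treatment is not the same as knowing the arm at a visit placed before randomisation.

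What does not stand is that nothing needs correcting. The article does name its concealment device, and that device does not fit the unit it randomises. This is a mismatch in stated text, not only an omitted detail.

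**Conclusion.** The concealment unit does not match the randomisation unit, and the passages must be reconciled. That conclusion rests on the article's own wording and needs no assumption about conduct.

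The size of any loss of concealment is conditional. It ranges from 0 of 80, if each cohort's assignment is opened only once the cohort is complete, to at most 72 of 80, if shared-arm envelopes are opened person by person in eight full cohorts of 10 (76 of 80 with the Abstract's four cohorts of 20). The documents do not settle where in that range the trial would lie, and they do not show that anyone is enrolled after the arm is known. The figure of 0.002 for the independent-assignment reading assumes simple 1:1 allocation.

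The correction is still worth making before enrolment: it is cheap, and lost concealment cannot be restored afterwards.

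**What to change.** In the Randomisation section, replace the individual envelopes with one sealed assignment per cohort, held by the trial statistician or another person not involved in recruitment. State that it is released only after every member of that cohort has consented, passed the eligibility examination, stated a treatment preference and completed baseline outcomes, and that the cohort is closed to further entry from then on. While editing, bring the number and size of cohorts in the Abstract and in Sample size into agreement, since these set the number of sealed assignments needed.

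The cost is a few sentences and scheduling baseline visits by cohort, which the week 1 to week 7 timetable already largely implies. No extra participants are required. The downside is that some people wait until their cohort is complete.
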